## 14 APPENDICES

### 14.1 ADVERS EVENTS: DEFINITIONS AND PROCEDURES FOR RECORDING, EVALUATING, FOLLOW-UP, AND REPORTING

#### 14.1.1 DEFINITION OF ADVERSE EVENTS (AE)

An adverse event (AE) is defined as the development of any untoward medical occurrence in a patient / study participant administered a medicinal product / intervention and which does not necessarily have a causal relationship with this treatment. An AE can therefore be any unfavourable and unintended sign (for example an abnormal laboratory result) and symptom (for example nausea, pain), or disease temporally associated with the use of a medicinal (investigational) product / intervention, whether or not related to the medicinal (investigational) product / intervention.

AE includes complaints reported by the patient (patient interview), abnormalities found during the patient's examination (physical examination), or ancillary examinations (abnormal laboratory tests, findings in radiological examinations).

The term AE includes both serious and non-serious AEs and can include a worsening / deterioration (for example an increase in their frequency, intensity, or severity) of a medical condition pre-existing (including chronic diseases) before inclusion in the study. An AE may occur at any time, including screening even when no study treatment has been administered.

In this study AEs will be reported and recorded in the appropriate eCRF section from the moment of obtaining informed consent until end of study (Visit 6; End of Study).

#### 14.1.2 DEFINITION OF SERIOUS ADVERSE EVENTS (SAE)

A serious adverse event (SAE) is defined as an AE occurring during the study that fulfils one or more of the following criteria:

- Results in death
- Is (immediately) life-threatening,
- Requires in-patient hospitalization or prolongation of existing hospitalization,
- Results in persistent or significant disability/incapacity, or
- Is a congenital anomaly or birth defect
- Is an important medical event that may jeopardise the patient or may require medical treatment to prevent one of the outcomes listed above

##### **Notes / additional explanations:**

##### Life-threatening

“Life-threatening” means that the patient / study participant was at immediate risk of death from the AE as it occurred, or it is suspected that use or continued use of the product would result in the patient's death. “Life-threatening” does not mean that the patient / study participant had an AE in a more severe form

##### Hospitalisation

Outpatient treatment in an emergency room is not in itself a serious AE (SAE), although the reasons for it may be (e.g., bronchospasm, laryngeal oedema). Hospital admissions and/or surgical operations planned before or during a study are not considered AEs, if the illness or disease existed before the patient was enrolled in the study and providing that it did not deteriorate in an unexpected way during the study.

##### Important medical event

Important medical event means an AE that may not be immediately life-threatening or result in death or hospitalisation but may jeopardise the subject or require medical or surgical intervention to prevent one of the outcomes listed for SAE.

#### 14.1.3 EVENTS OF SPECIAL INTEREST

Events of Special Interest (ESI) are those events thought to be associated, or potentially associated with the investigational treatment and/or AIS course. In the STROACT study there are prespecified AEs / events which are considered as ESI. These events will be monitored during the study and will be analysed as the critical safety endpoints comparing the study treatment and placebo groups.

- Mortality at 7-, 30- and 90-days post AIS:
- Neurovascular events at 7-, 30- and 90-days post AIS:
  - Recurrent ischaemic stroke
  - Neurological deterioration (NIHSS)
- Incidence of intracranial bleeding (symptomatic and asymptomatic) assessed with CT/MRI and assessed according to European Cooperative Acute Stroke Study (ECASS II) classification at 24h and 7 days after study treatment administration.
- Incidence and severity of major extracranial haemorrhage defined as:
  - fatal
  - severe enough to require transfusion or operation
  - an absolute decrease in haemoglobin > 5 g/dL
  - a decrease in haematocrit of > 15%
  - bleeding associated with persistent or serious disability)
- Post-treatment thromboembolic and cardiovascular events.

#### 14.1.4 ADVERSE REACTION (AR)

Adverse reaction (AR) to an investigational medicinal product is defined as all untoward and unintended responses to an investigational medicinal product related to any dose administered. All adverse events judged by either the reporting investigator or the sponsor as having a reasonable causal relationship to a medicinal product qualify as adverse reactions. The expression reasonable causal relationship means to convey in general that there is evidence or argument to suggest a causal relationship.

#### 14.1.5 SUSPECTED UNEXPECTED SERIOUS ADVERSE REACTION

A Suspected Unexpected Serious Adverse Reaction (SUSAR) is defined as an untoward and unintended response to a study drug, which is not listed in the applicable product information, and meets one of the following serious criteria: results in death, is life-threatening, requires hospitalisation or prolongation of an existing hospitalisation, results in persistent or significant disability or incapacity, or is a congenital anomaly or birth defect.

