#### 9.3.1.4 EXPECTEDNESS

Expectedness assessment is deciding whether the adverse event presented is listed (expected) or not listed (unexpected) in the appropriate section of the SmPC.

Suspected Unexpected Serious Adverse Reactions must be reported in an expedite manner to regulatory authorities, and also assessed by the IDMC.

For definition of Suspected Unexpected Adverse Drug Reaction please refer to Appendix [Section 14.1.5](#)

---

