#### 10.3.3 INDEPENDENT DATA MONITORING COMMITTEE

An Independent Data Monitoring Committee (IDMC) will be appointed before study start, and will be responsible for ensuring patient safety, by estimating the benefit-risk balance during the study, for the overall conduct of the study and for reporting to the study EC.

The IDMC will analyse periodically and on an ongoing basis incoming safety data (i.e., safety endpoints, serious adverse events, premature withdrawals from the study due to the adverse event), and efficacy data both overall and for individual centres.

In the event of safety concerns which would require a change in the study conduct, the DMC is obliged to report this incident to the study EC.

Details of IDMC responsibilities and operating procedures will be provided in IDMC Charter.

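### The SUSAR definition omits the important-medical-event criterion, so reactions serious only on that ground fall outside expedited regulatory reporting and the SUSAR-specific IDMC assessment

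*Protocol*

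**What the plan says.** The protocol defines seriousness in three places: Section 9.3 (SAE definition), Section 9.3.1.1 (seriousness assessment) and Appendix 14.1.2. All three end their list with the same item: "Is an important medical event that may jeopardise the patient or may require medical treatment to prevent one of the outcomes listed above". The notes to 14.1.2 explain what it is for: "Important medical event means an AE that may not be immediately life-threatening or result in death or hospitalisation".

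The SUSAR definition in Appendix 14.1.5 does not refer to those lists. Besides being absent from the product information, the reaction must satisfy one item of a fixed list, namely that it "results in death, is life-threatening, requires hospitalisation or prolongation of an existing hospitalisation, results in persistent or significant disability or incapacity". A fifth item, on congenital defects, closes that list. The important medical event does not appear.

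Section 9.3.1.4 sets out what follows from SUSAR status: "Suspected Unexpected Serious Adverse Reactions must be reported in an expedite manner to regulatory authorities, and also assessed by the IDMC". For the meaning of the term it points to the appendix ("For definition of Suspected Unexpected Adverse Drug Reaction please refer to Appendix", with a link to 14.1.5).

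Two other rules apply to every SAE, SUSAR or not. Section 9.3.3 requires it to be reported to the CRO immediately and within 24 hours. Section 10.3.3 gives the IDMC both regular and continuous review of "incoming safety data (i.e., safety endpoints, serious adverse events, premature withdrawals from the study due to the adverse event").

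**The concern.** One protocol gives the word serious two meanings, and the narrower one governs expedited reporting. The criterion left out is the one meant to catch events that the others miss.

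The gap has some weight in this trial. Visits 0 to 3 are expected to take place in hospital (Section 1.3, note d), so initial hospitalisation cannot mark an in-hospital reaction as serious in the first week; only prolongation can. Patients also enter with a disabling deficit (Section 5.1, criterion 3), which makes disability caused by a reaction harder to separate from the stroke. Section 2.3 describes the study as the first of this sequential therapy, and Section 2.3.2 says there are no empirical data for andexanet alfa followed by rtPA. Early notice of unexpected reactions is what expedited reporting is for.

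**Working it through.** No sample size, error rate or event count bears on this point, so the check compares the definitions and then follows each reporting route.

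**Step 1. The seriousness criteria in the four places**

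| Criterion | 9.3 | 9.3.1.1 | 14.1.2 | 14.1.5 (SUSAR) |
|---|---|---|---|---|
| Death | yes | yes | yes | yes |
| Life-threatening | yes | yes | yes | yes |
| Hospitalisation or its prolongation | yes | yes | yes | yes |
| Persistent or significant disability or incapacity | yes | yes | yes | yes |
| Congenital anomaly or birth defect | yes | yes | yes | yes |
| Important medical event | yes | yes | yes | **no** |
| Count | 6 | 6 | 6 | 5 |

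The difference is 6 − 5 = 1 criterion, the important medical event.

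**Step 2. Is the shorter list open or closed?** It is closed. The wording requires one of the criteria that follow, gives no indication that they are examples, and has no cross-reference to 14.1.2.

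**Step 3. Which definition governs?** Section 9.3.1.4 states the expedited-reporting duty and refers to 14.1.5. Section 9.3.3, on determining expectedness, also points to 9.3.1.4 and 14.1.5. The five-item list is therefore the operative one.

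**Step 4. Trace one case.** Take a suspected, unlisted reaction that meets the sixth criterion and none of the other five.

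| Route | Depends on | Does the case qualify as written? |
|---|---|---|
| Report to the CRO within 24 hours (9.3.3) | SAE status | Yes |
| Ongoing IDMC review (10.3.3) | SAE status | Yes |
| Expedited report to authorities (9.3.1.4) | SUSAR status | No |
| SUSAR-specific IDMC assessment (9.3.1.4) | SUSAR status | No |

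Two routes stay open and two close.

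**Step 5. Size.** The protocol gives no rate of suspected unexpected reactions and no share that would be serious on this ground alone, so the number affected cannot be estimated.

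**The case against.** The strongest reply is that little is lost in practice. The event still reaches the CRO within 24 hours, and Section 9.3.3 asks for expectedness to be determined as soon as possible. The IDMC reviews SAEs with no SUSAR filter and has access to unblinded data (Section 7.3.3). Section 10.4 delegates regulatory safety reporting to a CRO, Section 12.1 binds the study to applicable law and GCP, and the Safety Management Plan (Sections 1.1.10.2 and 12.1.7) is not available here. Safety staff may well apply the full six criteria.

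Most of this stands, and it rules out several stronger readings:

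- A reader might infer that these reactions escape the IDMC. They do not; Section 10.3.3 brings them in as SAEs. Only the assessment triggered by SUSAR status is lost.
- A reader might infer that reports would in fact go unmade. The documents show only that the definition, read literally, is too narrow.
- A reader might think first of allergic reactions or thromboses. Significant allergic reactions are a safety endpoint reviewed from Visit 1 onward (Section 1.3, note w; Sections 6.5.2 to 6.5.6), and thromboembolic events are Events of Special Interest (Sections 9.2.1 and 14.1.3). Neither is shown to be absent from the product information, as a SUSAR must be. Section 2.3.1 itself reports thrombotic events after both antidotes (6.56% and 10%), and a thrombosis might also qualify by prolonging the hospital stay.
- A reader might turn one criterion in six into a share of events. That counts list items and says nothing about frequency. Nor does any passage show that the sixth criterion is the one most often met.

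What the reply does not do is repair the text. Other safeguards do not remove the contradiction between 14.1.5 and 14.1.2, and a protocol should not rely on its users overriding its own definition.

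**Conclusion.** The point holds as an internal inconsistency in the safety-reporting definitions. A suspected, unexpected reaction that is serious only as an important medical event is an SAE under Sections 9.3, 9.3.1.1 and 14.1.2 but not a SUSAR under 14.1.5. As written, it lies outside expedited reporting to authorities and outside the SUSAR-specific IDMC assessment in Section 9.3.1.4. It remains inside 24-hour CRO reporting and the general IDMC review of SAEs.

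This rests on a literal reading of a closed list and on the cross-reference from 9.3.1.4; an unseen Safety Management Plan could be wider, but the protocol would still contradict itself. The number of events concerned is unknown and may be small. Sample size, error rates and the primary analysis are untouched. It is a minor correction that is worth making.

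**What to change.** In Section 14.1.5, delete the five-item list and state instead that the reaction must meet any of the SAE criteria in Section 14.1.2. Seriousness then has one definition throughout, and Section 9.3.1.4 needs no change because it already refers to 14.1.5. If the Safety Management Plan repeats the SUSAR definition, check that it matches.

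The cost is one line of text and possibly a few more expedited reports. Design, data collection and analysis do not change.

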#### 14.1.6 ASSESSMENT OF ADVERSE EVENTS

The National Cancer Institute CTCAE latest version (CTCAE version 5.03) will be used for assessing AE intensity (severity of event) for all events with an assigned CTCAE grading. For those events without assigned CTCAE grades, the recommendation in the CTCAE criteria on converting mild, moderate, and severe events into CTCAE grades should be used.

A copy of the CTCAE can be downloaded from the website <http://ctep.cancer.gov>.

#### 14.1.6.1 SEVERITY OF EVENT

#### 14.1.6.2 RELATIONSHIP TO STUDY INTERVENTION

The investigator will assess causal relationship between drug / study intervention and each AE. Assessing causality (relationship to study intervention) the following factors when deciding if there is a “reasonable possibility” that an AE may have been caused by the drug / intervention should be considered:

- Time Course / Exposure to suspect drug.  
*(Has the patient actually received the suspect drug? Did the AE occur in a reasonable temporal relationship to the administration of the suspect drug?)*
- Consistency with known drug profile.  
*(Was the AE consistent with the previous knowledge of the suspect drug [pharmacology and toxicology] or drugs of the same pharmacological class? Or could the AE be anticipated from its pharmacological properties?)*
- De-challenge experience.  
*(Did the AE resolve or improve on stopping or reducing the dose of the suspect drug?)*
- No alternative cause.  
*(The AE cannot be reasonably explained by another aetiology such as the underlying disease, other drugs, other host or environmental factors.)*
- Re-challenge experience.  
*(Did the AE reoccur if the suspected drug was reintroduced after having been stopped?)*
- Laboratory tests. A specific laboratory investigation (if performed) has confirmed the relationship.

## 14.2 PERFORMANCE AND FUNCTIONAL ASSESSMENT FORMS

### 14.2.1 NIHSS ASSESMENT FORM

The Polish version of the Barthel Index Assessment Form.

Skala Udarów Narodowego Instytutu Zdrowia  
National Institutes of Health Stroke Scale (NIHSS)

**Data:**  
**Godzina:**

|                                                                                                                                                                                                                                                                                                                                                                                                                                                                                                         |  |  |  |  |  |
|---------------------------------------------------------------------------------------------------------------------------------------------------------------------------------------------------------------------------------------------------------------------------------------------------------------------------------------------------------------------------------------------------------------------------------------------------------------------------------------------------------|--|--|--|--|--|
| 1A. Poziom świadomości
- pełna, chory czuwający 0
- chory podsypany, wybudza się przy niewielkiej stymulacji SOMNOLENCJA 1
- chory głęboko senny, w celu wybudzenia konieczne wzmocnienie bodźca lub bodziec bolesny STUPOR 2
- śpiączka (prężenia ruchowe i/lub odruchy autonomiczne, wzgl. brak reakcji) 3                                                                                                                                             |  |  |  |  |  |
| 1B. Odpowiedź na pytanie o miesiąc i wiek (liczy się pierwsza odpowiedź)
- prawidłowa na oba pytania 0
- prawidłowa na jedno lub dyzartria, intubacja, bariera językowa 1
- obie nieprawidłowe lub brak odpowiedzi 2                                                                                                                                                                                                                                               |  |  |  |  |  |
| 1C. Spełnianie poleceń (zamknięcia lub otwarcia oczu, oraz wyprostowania lub zgięcia palców ręki)
- spełnia oba 0
- spełnia jedno 1
- nie spełnia żadnego 2                                                                                                                                                                                                                                                                                                        |  |  |  |  |  |
| 2. Zbaczanie głowy i gałek ocznych (ruchy gałek ocznych w prawo i w lewo)
- brak zbaczania, ruchy gałek w pełnym zakresie 0
- częściowe zbaczanie gałek ocznych, nieutrwalone, ustępujące przy manewrze oczno-głowym 1
- utrwalone zbaczanie, nieustępujące 2                                                                                                                                                                                                      |  |  |  |  |  |
| 3. Pole widzenia (prezentacja bodźca w poszczególnych kwadrantach pola widzenia)
- bez ubytków 0
- częściowe niedowidzenie połowicze (np. kwadrantowe) 1
- pełne niedowidzenie połowicze 2
- ślepotą (np. korową) lub obustronne niedowidzenie połowicze 3                                                                                                                                                                                               |  |  |  |  |  |
| 4. Czynność nerwu twarzowego (pacjent proszony o uśmiech, uniesienie brwi, zaciśnięcie powiek)
- symetria twarzy zachowana 0
- nieznaczne wygładzenie fałdu nosowo-wargowego, asymetria przy uśmiechu 1
- wyraźne obniżenie kącika ust 2
- porażenie mięśni połowy twarzy (jedno- lub obustronnie) 3                                                                                                                                                     |  |  |  |  |  |
| 5. Siła mięśniowa kończyny górnej (uniesienie wyprostowanej kończyny przez 10 sekund)
- gdy utrzymuje kończynę pod kątem 45° przez 10 sekund (także amputacja lub patologia stawu) 0
lewa
- gdy kończyna zaczyna opadać przed upływem 10 sekund 1
- nie utrzymuje kończyny w poziomie, ale widoczny jest opór przeciw sile ciężkości 2
prawa
- kończyna opada natychmiast, ślad ruchu 3
- całkowity brak ruchów czynnych 4 |  |  |  |  |  |
| 6. Siła mięśniowa kończyny dolnej (uniesienie wyprostowanej kończyny przez 5 sekund)
- gdy utrzymuje uniesioną pod kątem 30° przez 5 sekund (także amputacja lub patologia stawu) 0
- gdy kończyna powoli opada przed upływem 5 sekund 1
lewa
- opada szybko przed upływem 5 sek., lecz zachowany jest opór przeciw sile ciężkości 2
prawa
- opada natychmiast, ślad ruchów 3
- całkowity brak ruchów czynnych 4           |  |  |  |  |  |

|                                                                                                                                                                                                                                                                                                                                                                                                       |  |  |  |  |  |
|-------------------------------------------------------------------------------------------------------------------------------------------------------------------------------------------------------------------------------------------------------------------------------------------------------------------------------------------------------------------------------------------------------|--|--|--|--|--|
| 7. Ataksja (próba palec-nos, pięta-kolano)
- brak (także amputacja, patologia stawu, niedowład lub brak rozumienia) 0
- obecna w kończynie górnej lub dolnej 1
- obecna w obu kończynach 2                                                                                                                                                                       |  |  |  |  |  |
| 8. Czucie (badane przez ukłucie w zakresie twarzy, kończyn, tułowia), gdy afazja lub stupor 0 lub 1 pkt.
- prawidłowe 0
- zaburzenia w stopniu niewielkim lub umiarkowanym, tj. osłabienie czucia bólu lub ukłucie odczuwalne jako tępe, ewent. pacjent odczuwa tylko dotyk 1
- znacznie osłabione, lub brak (także śpiączka i/lub porażenie czterokończynowe) 2 |  |  |  |  |  |
| 9. Język (nazywanie przedmiotów, opisanie obrazu, czytanie/powtarzanie tekstu)
- bez zaburzeń 0
- błędne nazywanie, niezdolność do dobierania właściwego słowa „parafazje”, lub/i zaburzenia rozumienia 1
- zaburzenia znacznego stopnia: w pełni rozwinięta afazja typu Broca lub Wernickego (ewent. inny rodzaj) 2
3                                 |  |  |  |  |  |
| 10. Dyzartria (wymowa, czytanie względnie powtarzanie słów)
- brak (także intubacja lub brak możliwości zbadania) 0
- umiarkowana, rozumiany z trudem „bełkocze”, możliwa komunikacja werbalna 1
- znacznego stopnia, słowa całkowicie niezrozumiałe, mutyzm 2                                                                                                   |  |  |  |  |  |
| 11. Zespół nieuwagi połowicznej (modalność wzrokowa, słuchowa, czuciowa, przestrzenna, osobowa)
- bez zaburzeń 0
- wygaszanie bodźca jednego rodzaju (czucia, słuchu, wzroku) 1
- nasilone objawy/ wygaszanie więcej niż jednego rodzaju bodźców 2                                                                                                               |  |  |  |  |  |
| Wynik badania:                                                                                                                                                                                                                                                                                                                                                                                 |  |  |  |  |  |
|                                                                                                                                                                                                                                                                                                                                                                                                       |  |  |  |  |  |

